#### **5.7.e. Specific Aim 3 (Sustainability Analysis)**

##### **Survey and Interview Administration and Analysis of Implementation Data**

Those agreeing to participate will receive a REDCap invitation to complete the PSAT. PSAT allows users to: (1) understand factors associated with sustainability; (2) assess the sustainability of a program; (3) review their sustainability report, and; (4) develop an action plan to enhance the chances of programmatic sustainability. Participating staff at WAVE 1 and 2 sites will receive invitations to complete the online instrument at three time points: at baseline, at the end of active implementation, and at the end of sustainability. WAVE 3 sites will complete the PSAT at baseline and at the end of implementation. This tool assesses the facility's overall capacity for sustainability and across the specific domains of: environmental support, funding stability, partnerships, organizational capacity, communications, and strategic planning. Reports are generated by this tool, ranking the facility from 1 (little to no extent) to 7 (to a great extent) and provides guidance on what areas can be addressed to maximize sustainability. Of note, as reflected in our letters of support from our site co-investigators, they have obtained support and commitment from their institutions and did not score below a 5.0 on their PSAT report. Telephone or virtual interviews will be conducted in after the final PSAT has been completed

and at the end of sustainability for sites within WAVE 1 and WAVE 2. We intend to conduct phone or virtual interviews among seven ASAP end users at each of the six sites. Guided by the Dynamic Sustainability Framework, we will both conduct interviews among ASAP end users regarding the intervention, contextual elements of implementation, and the VAMCs instituting ASAP, with special attention to sustainability constructs of time, continued delivery, behavior change, evolution, and continued benefit. Examples of interview questions will include: What activities have you yourself participated in terms of implementing the local ASAP program? What would you say are the strengths of how the program has been implemented? What barriers have you and/or the team faced during making improvements in sleep apnea care? How did you overcome these barriers? How confident are you that ASAP will be sustained at your local VAMC? Why or why not? What local resources have been secured or provided for ASAP? What additional resources are still needed to sustain ASAP at your facility? PSAT data will be added to the NVivo project files containing the tagged qualitative interview data, the scored construct data, the standardized ORCA data, the categorical data, and the quantitative outcome data, and analyzed to understand barriers and predictors of sustained use of ASAP and to understand how intervention components, implementation strategies and local context influence sustainability. We hypothesize that sustainability will be greatest at sites that use HST as their primary approach and have champions who engage with systems redesign staff and perform at least quarterly implementation activities. To estimate if the diagnostic rate continues through the sustainability phase, the effect for sustainability will be estimated from the primary outcome models.

#### **5.7.3. Specific Aim 4 (Business-Case Analysis)**

**Business-Case Analysis Overview** We will construct a business-case analysis that involves a comparison of the ASAP program with the current standard practice. If staff time data collected from the sites is adequate, we will construct a business-case analysis at each of the participating sites as well as an aggregated (overall) business-case analysis. We will meet with the facility leadership for participating sites at the beginning of the study and confirm that the proposed business-case analysis includes all of the key financial elements that are of interest to the facility leadership. We will also ask whether there are important non-financial considerations that would inform a decision about whether to invest in the ASAP program. For example, for some interventions, key non-financial aspects can be so important to facility leaders that they need to be considered in a business-case analysis (e.g., improved clinic access). We do not anticipate that the ASAP program will involve elements not able to be translated into financial terms, and hence our primary plan is to focus on financial elements only. Involving facility leadership in the development of the business-case analysis serves two key functions: it ensures that the analysis includes elements that may not have been apparent to the research team members and it strengthens buy-in for the program with the key stakeholders. This latter issue is of relevance to implementation

projects where the goal is to ensure strong leadership support for program implementation and sustainability like ASAP.

| Table 5. Data Elements and Sources Related to Business-case Analysis |                                                                                                                                                                                                                                                                                                                                                        |
|-----------------------------------------------------------------------------|--------------------------------------------------------------------------------------------------------------------------------------------------------------------------------------------------------------------------------------------------------------------------------------------------------------------------------------------------------|
| Data Element                                                         | Data Sources                                                                                                                                                                                                                                                                                                                                    |
| Staff time (training)                                                       | Locality-specific staff pay rates will be obtained from Financial Management System (FMS), MCA, and Account-Level Budgeter Cost Center (ALBCC) databases; Staff participants will maintain a diary of time spent in training—an average time will be used for the main analysis and extreme values will be used in sensitivity analyses                |
| Staff time (implementation)                                                 | Surveys of participants involved in ASAP implementation                                                                                                                                                                                                                                                                                                |
| Equipment: PSG-related                                                      | Will include any one-time costs (e.g., PSG equipment purchases) and also incremental per-patient costs associated with disposable items (e.g., gloves, tape). Costs will be obtained from prices that are paid by the sites and as above the average cost will be used for the main analysis. and extreme values will be used in sensitivity analyses. |
| Total healthcare costs for one-year pre- and post-index event               | Total healthcare costs (inpatient and outpatient) for the individual patients will be obtained from MCA data. All costs will be converted to the same fiscal year (to adjust for temporal differences in the waves).                                                                                                                                   |

The business-case analysis will focus on financial costs and savings. We will include all of the ASAP program costs (Table 5) including: staffing and training costs (obtained by staff surveys about time allocations for specific activities which will be converted to staffing costs), equipment costs (obtained by sleep medicine service surveys), and supply costs (obtained by site PI surveys); patient travel reimbursements (if patients are traveling to the VA to obtain sleep services; obtained from VSSC Beneficiary Travel report); and total patient health care costs for inpatient and outpatient utilization (obtained from the VHA Managerial Cost Accounting [MCA] System). We do not expect that the ASAP program will involve changes in space, but if any of the participating sites requires changes in space this will be included in the analysis. We will not include any research-specific costs. The business-case analysis will be built from the VAMC leadership perspective and will therefore not include patient costs. The timeframe for the business-case analysis will be the active implementation phase and no discounting will be performed. If data availability allows, we will compare the business-case analyses across the 6 participating sites. The primary comparison will involve assessing differences between intervention patients versus usual care patients. Veterans Equitable Resource Allocation (VERA) reimbursements will not be considered in the primary business-case analysis because all the patients in the ASAP program have had a stroke or TIA and the intervention is unlikely to influence VERA classification or reimbursements, although we will ask site leadership regarding including VERA in the analysis. The final product of the business-case analysis will be a report and will include the estimated per patient cost for ASAP program implementation and differences in the estimated costs for intervention versus usual care patients. Cost data will only involve data from ASAP sites. As we anticipate that the ASAP program will reduce recurrent vascular events, we hypothesize that the business-case analysis will favor the intervention at sites with the highest baseline recurrent vascular event rate, reducing costs associated with relatively expensive readmissions.

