**CLINICAL RELATIONSHIPS:** Interventions that improve diagnosis and management of OSA among Veterans with stroke/TIA are necessary to improve outcomes; implementation science strategies can assess the uptake and sustainability of this intervention. Because the intervention and implementation strategies have been designed using existing VHA infrastructure, if effective, the program would be ready for scaling system wide. Results from the business-case analysis for ASAP will be shared with VAMC providers and local leadership who may be interested in implementing this program at their facility. Additionally, an acute sleep service could be adapted to other patient populations (e.g., chronic obstructive pulmonary disease), both within and outside of VHA.

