**Data Monitoring** Chart review will be conducted centrally (Indianapolis VAMC/West Haven VAMC) and at the local sites. Chart review will be conducted on all eligible ischemic stroke and TIA patients who are admitted at the participating sites. Patients with ischemic stroke/TIA will be identified using ICD-10 codes in the Corporate Data Warehouse (CDW). The hub will include facility-level data for: OSA diagnosis and ASAP primary and secondary effectiveness outcomes. The hub allows sites to compare their data to other sites and to examine trends over time. Site staff/providers will use these data to iteratively improve ASAP implementation. For example, if sites learn that OSA testing rates are lower after discharge than during the hospitalization period, processes focusing on hospitalized (rather than discharged) patients would be appropriate. To complement data seen on the Hub, the results of the chart review will be provided to implementation sites and will be discussed at the Virtual Collaborative monthly conferences. Furthermore, recognizing that each patient is an opportunity to improve local ASAP processes and procedures, during external facilitation sessions, patient-level data will be reviewed with the sites.

**5.1.d. Implementation Strategy** This project draws explicitly upon the implementation strategies of external facilitation and data and feedback, which will be assessed on an ongoing basis over the intervention period.

**External Facilitation** External facilitation changes over time based on the needs of the team. However, the core elements of relationship-building, methods training, communication, facilitating team-based problem solving, and monitoring performance over time will be preserved through external facilitation from a Lean Six Sigma Black Belt experienced in stroke QI work and ASAP investigators experienced in implementation of post-stroke/TIA OSA programs.

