## Notes from Interactions the ASAP Research Team has with Champions and Others Involved in Local Implementation of QI ASAP Initiatives

**External Facilitation** interactions between ASAP Research personnel and local site personnel performing ASAP QI will include on average a monthly scheduled meeting as well as *ad hoc* interactions that occurs at the request of either local teams or ASAP Research personnel. Number of minutes by participant by type of contact will be recorded in an external facilitation tracker and notes from these interactions will be recorded in on a standardized external facilitation interaction template

**Monthly Collaborative Calls** will produce a combination of data which includes triumphs and barriers, lessons learned from the prior month, and short- and longer-term implementation goals reported by sites, notes taken by ASAP Research personnel, and an ASAP Research-personnel debrief that is recorded and transcribed after ASAP Collaborative calls

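### The business case promises every ASAP programme cost, but centrally delivered facilitation and feedback have no entry, so the per-patient cost of the programme as delivered is understated.

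*Protocol*

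**What the plan says.** On scope, section 5.7.3 states: "We will include all of the ASAP program costs (Table 5) including: staffing and training costs". The same paragraph goes on to equipment, supplies, patient travel reimbursement, total healthcare costs and, if needed, space. Table 5 has four rows: staff time for training, staff time for implementation, PSG-related equipment, and healthcare costs in the year before and after the index event. The implementation-time row has one source: "Surveys of participants involved in ASAP implementation".

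On limits, the section says "We will not include any research-specific costs" and sets the viewpoint: "The business-case analysis will be built from the VAMC leadership perspective and will therefore not include patient costs". The final report "will include the estimated per patient cost for ASAP program implementation", and the Abstract gives its audience: "Results from the business-case analysis for ASAP will be shared with VAMC providers and local leadership who may be interested in implementing this program".

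On what is delivered, Specific Aim 1 in section 2 says that ASAP includes two implementation strategies, external facilitation and audit and feedback. Section 5.1.d describes the first as "external facilitation from a Lean Six Sigma Black Belt experienced in stroke QI work and ASAP investigators", and has active sites receive feedback every month. Section 5.6 says of facilitation contacts: "Number of minutes by participant by type of contact will be recorded in an external facilitation tracker".

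**The concern.** A programme cost that is meant to inform adoption should count the inputs that produced the measured effect. Part of what the six sites receive comes from a central team, and the cost plan shows no place where that team's time is counted. If it stays out, the savings attributed to ASAP come from sites that had central support, while the cost set against them omits that support. The error has a known direction: it makes ASAP look cheaper than it was. A facility leader outside the trial who relies on the per-patient figure would not see that some of the effort was supplied from elsewhere, or what replacing it would cost.

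**Working it through.** The protocol states no cost figure, so there is none to reproduce. The check compares what is delivered with what is costed.

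**Delivered inputs and their cost entry**

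| Input | Where described | Cost entry in 5.7.3 |
|---|---|---|
| Site staff training time | Table 5 | Yes (diary) |
| Site staff implementation time, including time in facilitation and feedback meetings | 5.1.c, 5.1.d | Can enter under the general implementation row |
| PSG equipment and supplies | Table 5 | Yes |
| Patient travel, healthcare use | 5.7.3 | Yes |
| Time of the Black Belt and investigators as facilitators | 5.1.d, 5.6 | None |
| Central preparation of monthly feedback | 5.1.c, 5.1.d | None |

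**Could the central items enter by another route?** The named sources are staff surveys, sleep-service surveys, surveys of site principal investigators, prices that the sites paid, and VA travel and cost-accounting systems. The overview of 5.7.3 makes the site-level analyses depend on staff-time data gathered from the sites. A later sentence confines cost data to ASAP sites; it may be aimed mainly at control sites, but it opens no route for central time. The facilitation tracker is not named as a cost source.

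**Where does the exclusion fall?** 'Research-specific' is not defined. Section 5.6 describes external facilitation as contact between ASAP research personnel and local staff, and section 5.5.a makes even local site investigators and field staff members of the research team. Chart review supplies the feedback (5.1.c) and is also a study data source (5.6). The undefined term can therefore be read to cover the central work, although the protocol never says that it does.

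**Do benefit and cost cover the same thing?** The cost model under Specific Aim 4 uses the baseline and active implementation periods with an active-implementation indicator, and the business-case timeframe is the active phase. Facilitation meetings average one a month, and feedback is monthly to sites in that phase. The sustainability period is not in the model. The estimated effect on healthcare cost therefore belongs to the centrally supported programme.

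**Size.** The documents give no hours, central staffing or pay rates for these items, so the gap cannot be derived. A purely illustrative range for scheduled facilitation alone follows.

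- Eligible patients per site: 111 per year (5.1.b) × 21/12 = 194.
- Scheduled meetings: about one a month (5.6) over 21 months = 21.
- Assumed: 1 hour per meeting, 2 to 4 central staff, $60 to $100 per hour.
- Hours: 21 × 1 × 2 = 42 to 21 × 1 × 4 = 84 per site.
- Per patient: 42/194 = 0.22 h to 84/194 = 0.43 h.
- Cost: 0.22 × $60 = about $13 to 0.43 × $100 = about $43 per eligible patient.

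This leaves out ad hoc contacts, the kick-off, collaborative calls and feedback preparation. Chart review is also left out, because much of it is needed to ascertain outcomes in any case.

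**The case against.** The strongest reply is that this is an ambiguity and not an omission. The cost list is introduced as a set of inclusions and need not be exhaustive. The implementation row is general enough to hold site staff's time in facilitation calls and feedback reviews, and local chart abstraction too. Nothing expressly classes facilitation or feedback as research. A VAMC leadership perspective properly leaves out costs that a facility does not bear, and the Abstract describes the programme as built on what VHA already has. The team will also ask facility leaders at the outset whether key financial elements are missing. Finally, the stated hypothesis concerns which sites the business case favours, and a roughly uniform added cost would hardly change their order.

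Much of this stands. A reader might infer that both strategies enter at zero cost, or that the research exclusion bars them outright. The documents support neither reading: site time can be captured, and the exclusion is undefined. The point about the ordering of sites also stands.

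The reply does not supply a route for central time. An open-ended list helps only if some source could feed it, and all the programme-cost sources are site-side. The perspective does not settle the matter either, because the protocol does not say who would provide or pay for facilitation at a new facility. The leadership check involves only participating sites, which already receive the support.

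**Conclusion.** The point holds in a limited form. Section 5.7.3 promises all programme costs, but central facilitation and central feedback preparation, which are part of ASAP, have no cost entry. The per-patient cost of the programme as delivered is therefore understated, in ASAP's favour. This rests on reading the listed sources as the ones that will be used, and on the cost effect being estimated over the supported periods, as the protocol states.

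The size is unknown. The $13 to $43 above depends on assumed meeting length, staffing and pay, and nothing in the documents shows that it would reverse a business case that includes a year of total healthcare costs. It would also go too far to say that the reported cost is for a programme that the trial did not deliver: it is the cost of the tested programme without its central support. The primary effectiveness outcome is unaffected. The issue lies in Aim 4's main deliverable and is worth correcting before costs are compiled.

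**What to change.** 1. Add a row to Table 5 for central external facilitation time: minutes by participant from the existing tracker, multiplied by pay rates.
2. Add a row for central feedback preparation, limited to effort beyond what outcome ascertainment needs.
3. Define 'research-specific' as work done only for evaluation, for example interviews, CFIR and GO scoring, control-site data and outcome chart review.
4. Report the per-patient cost and the net result both with and without central support. Keep the VAMC leadership figure, and label each so that an adopting facility can see what it would have to supply or obtain.

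The cost is two table rows, one definition and one further calculation. Facilitation minutes are already recorded; feedback preparation time would need a simple log or estimate. The drawback is a somewhat less favourable programme cost.
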